### Inclusion Criteria

Children must have an educational classification of autism, verified using the Social Communication Questionnaire [51], a parent-reported measure. They must also exhibit challenging behaviors (ie, behaviors dangerous to the self or others, behaviors that interfere with learning and development, and behaviors that interfere with socialization). Examples include aggression, self-injury, escape behavior, property destruction, loud noises, and rigid or inflexible behavior (if at least one of the challenging behavior criteria mentioned previously applies).

Participants will be recruited from the School District of Philadelphia and private preschools or schools in the Philadelphia area using several recruitment methods including emailing teacher listserves or email lists, through the center participant registry, through the study’s expert advisory board, and through projects led by [name] or DM. We will also send Parent Permission-to-Contact forms home from school via students, along with the study flyer. If parents sign the form and send it back to school, we will reach out to them to invite them into the study. We also include a version of the flyer and Parent Permission-to-Contact form in Spanish. We may also use study flyers sent through various relevant organizations and listserves, newsletters, internet postings, social media (Facebook and Twitter), and other recruitment tools as needed, and we may attend parent workshops and autism-related events to recruit participants. If study participation is initiated by parents, after consenting parents, we will send the referral contact forms to schools via parents to recruit the child’s teachers or reach out to the schools directly to invite teachers to participate, after obtaining letters of support from school principals or directors, if required. Then, parents and teachers who agree to be contacted will be contacted by the research team to explain the study and invite them to participate. In addition, once teacher consent is completed, classroom aides will also be invited to participate. If no aides are available to participate, we will invite their speech therapist, occupational therapist, or any other educational team member identified by the parent or teacher.

To help characterize the children in the study, we will obtain the child’s IQ from their Individual Education Program, if this was derived from a standardized test battery. If such an IQ score is not available on the child’s Individual Education Program, the research team will administer the Stanford Binet Abbreviated Scales [52] test battery to obtain an IQ score.

### Materials

#### Overview of the KeepCalm App

The KeepCalm app is designed to be an interactive learning and data collection tool to facilitate a team approach to support emotion regulation in students. It integrates wearable HR tracking to identify and alert educators about heightened stress in their students and remind them about evidence-based strategies for de-escalating stress, supporting proactive coping, and preventing challenging behaviors. Refer to Figure 2 for the KeepCalm causal model, which shows that the pathway from stress to challenging behaviors via emotion dysregulation is “rescued” with the KeepCalm app, via teacher-assisted emotion regulation, whereby the teacher supports their student to reattain autonomic equilibrium (ie, physiological baseline or resting state) via stress communication (ie, child HR signaling to teacher), along with individualized recommendations about strategies to keep calm.

The KeepCalm app offers 3 innovations (to be tested) that address the 3 barriers described in the *Introduction* section (Figure 1). First, it incorporates physiological stress data into treatment delivery by capitalizing on recent advances in wearable biosensing [22,53,54]. The selected consumer-grade trackers are accurate [53,55,56] and have high technical reliability [55,57] for measuring HR (beats per minute) and HR variability (interbeat interval), making them inexpensive and scalable alternatives to medical-grade devices. In previous studies, we found that 85% of children on the autism spectrum will wear these trackers without complaint and rate them high on comfort and low on exacerbating sensory sensitivities [55,57].

Second, KeepCalm reminds teachers about child-specific strategies when physiological stress is detected. Computerized clinical decision support systems have been found to be related to higher fidelity in evidence-based practices and better patient outcomes among providers who work in chaotic environments, such as ambulatory clinic staff [58-61]. Despite the promise of this technology, such systems have not been linked with HR monitoring for decision support during behavioral interventions or therapy. The KeepCalm app gives pop-up notifications about top emotion regulation and behavior management strategies identified for each child and contains a comprehensive easy-to-access list of proactive and reactive strategies to support teacher training and ongoing in-class coaching in these strategies by the center’s teacher coaches. Additional coaching will be conducted as needed.

Third, it has a feature to track and tailor strategy recommendations based on stress reduction data. The app captures HR data before and after strategy implementation, allowing for calculation of physiological stress reduction based on each strategy. These data allow for the calculation of the “Top 3 Strategies” for each child. These are included in push notifications linked with HR alarms, accessible via an app dashboard, and sent to teams on a daily or weekly basis via email, so that everyone can stay up to date with which strategies work best for each child. Thus, the technology gives teachers a tool to assess strategy effectiveness in restoring emotion regulation. This is adaptive and will allow teachers to tailor future use of strategies, thus supporting personalized treatment.

This app is aligned with the strategic plan of the Interagency Autism Coordinating Committee [62], which calls for maximizing the potential for technology-based intervention supports to improve the lives of individuals on the autism spectrum and developing technology-based treatments deployable in community settings to increase treatment access. In addition, our previous pilot data from parents and children show that they think that an app using HR signaling could be “extremely useful” for managing stress in students on the autism spectrum; they “strongly agree” that such a system would help prevent challenging behaviors, and they “strongly agree” that this offers advantages over current practices [63]. Figure 3 shows the main features and design of the KeepCalm app.

The KeepCalm app offers several features designed to make it easy to know when and how to intervene with children to support their proactive coping and emotion regulation development.

**Figure 2 figure2:**
[figure not shown]
KeepCalm causal model.

**Figure 3 figure3:**
[figure not shown]
KeepCalm app design.

#### HR Stress Zone Tracking

The KeepCalm app pairs with selected commercially available HR trackers (refer to the *HR Trackers* section) that children wear to allow moment-by-moment physiological arousal tracking by educators. After recording a baseline HR for each child, educators are given pop-up notifications to alert them about moderate stress levels, along with individualized top strategies that can be used to reduce their stress. As HR is an index of stress levels [22-24], an increase in HR may index rising stress in children. HR above baseline (ie, HR at rest) is arranged in a stress zone rainbow in the KeepCalm app, with green representing baseline, yellow representing small increase in HR above baseline (+10%), orange representing medium increase in HR above baseline (+20%), and red representing large increase above baseline (+30%). Educators can track the child’s HR, so that they can intervene at moderate stress levels (ie, orange-zone HR) to prevent challenging behaviors associated with high stress levels or HR of approximately 30% above baseline [30] (ie, red-zone HR). In doing so, the educator creates emotion regulation learning opportunities for the child. Increase in HR may occur for other reasons, including increased physical exertion; however, accelerometry data movement thresholds ensure that increases in HR owing to child movement are not reflected in the HR stress zone tracking (refer to the *Offline Mode* section).

#### Individualized Child Behavior, Skills, Triggers, and Strategies Tracking

The KeepCalm app is designed to help educators and parents track children’s individualized education programs in a centralized manner. Teams can create custom profiles for each child for individualized tracking of challenging behaviors, skills, behavioral triggers and antecedents, and strategies for that child and sync data entry across the team.

#### Top Strategy Notifications

The KeepCalm app offers individualized “top strategy” suggestions from an up-to-date list of evidence-based strategies for supporting emotion regulation and preventing challenging behaviors in children on the autism spectrum. The top strategies are individualized for the child based on previous data collection and HR tracking and sent out when a child enters the orange or red stress zones.

#### Offline Mode

“Offline mode” is activated when a child’s average movement (acceleration) over the past 5 seconds is ≥1 m/s^2^. This threshold was selected to screen out the effect of vigorous movement on the top strategy notifications triggered by the child entering the orange or red stress zones.

#### Evidence-Based Strategy Resources

The app provides resources (infographics and videos) about the implementation of evidence-based strategies to help support emotion regulation and prevent challenging behaviors in children on the autism spectrum. These strategies are based on the research team’s comprehensive systematic review of the literature [64].

#### Day View

The KeepCalm app includes a “Day View” tab with a daily report including 2 versions. The first is a detailed day view that includes each data entry in list and figure format, and the second is a summary day view that includes a narrative description of the day including the top strategies used that day. This downloadable report is autogenerated at the end of each day and sent to the team via pop-up notification to support frequent team communication.

#### Custom Reports

The KeepCalm app includes a “Reports” tab where teams can produce clear and concise tables and figures to present data about each child’s challenging behaviors, skills, behavioral triggers and antecedents and strategies for upcoming education team meetings and to share with parents. These downloadable reports may be used to help with noticing trends and for evidence-based programming to support children’s development.

#### Functional Behavioral Assessment Mode

The KeepCalm app includes a functional behavioral assessment mode to help teams collect data to determine the function of or reason for new or emerging challenging behaviors, to help decide on strategies for these behaviors. Behavioral analysts can be added to the child’s KeepCalm team for easy sharing of functional behavioral assessment data.

#### Team Messaging

The KeepCalm app offers a team messaging platform to aid team communication, which is important for consistency of strategy use across school teams and at home. Teams can also contact the app development team in real time for troubleshooting.

To sign up to the app, school personnel and parents will enter their name, email, phone numbers, and their child’s nickname or ID, so that they can identify the child. Teams will record triggers, behavior and skills, and strategies in the app, and HR and accelerometry data will be recorded from child participants. Only the child’s team members and the research team will have access to this information. The app does not collect any other information from participants’ mobile devices.

#### HR Trackers

We will use 2 HR tracker models previously tested for accuracy, reliability, validity, and comfort [55]—the Mio Fuse (Mio Global) wristband and Polar H7 (POLAR) chest strap. These models are highly accurate (correlation with wired electrocardiogram: Mio Fuse: mean *r*=0.91, 95% CI 0.882-0.929; Polar H7: mean *r*=0.99, 95% CI 0.987-0.991) [53,56] and reliable (they meet quality thresholds on spike rate—Mio Fuse: 100%; Polar H7: 87.4%-89.4% and sampling fidelity—Mio Fuse: 96.2%-97.1%; Polar H7: 96.6%-100%) [55] for measuring HR and HR variability. We found that children on the autism spectrum rated both devices in the comfortable range [55], and in our pilot study, they were able to wear one of the 2 HR trackers during 5 school days.

#### Accelerometer

We will also use belt-clip accelerometers (mBient MetaMotionRL or another suitable model) to measure child movement, so that stress zone alerts are not sent out during period of high child movement but instead put the child’s notifications in “offline mode” (refer to the *Offline Mode* section for more details). In our pilot study, teachers were asked to use the mBient trackers with child participants during 5 school days.

### Measures

#### Primary Outcome Measures

##### Usability

Teacher and parent perceptions of usability will be measured using the System Usability Scale [65]. The scale consists of 10 items rated on a 5-point Likert scale ranging from 1 (“Strongly disagree”) to 5 (“Strongly agree”). Responses are transformed to obtain a total value from 0 to 100, with higher scores indicating greater perceptions of usability. This scale will be administered at the end of the trial, 3 months after baseline.

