**Methods:**

We will test KeepCalm with 20 educational teams of students on the autism spectrum with challenging behaviors (no exclusion based on IQ or speaking ability) in a pilot randomized waitlist-controlled field trial over a 3-month period. We will examine the usability, acceptability, feasibility, and appropriateness of KeepCalm as primary outcomes. Secondary preliminary efficacy outcomes include clinical decision support success, false positives or false negatives of stress alerts, and the reduction of challenging behaviors and emotion dysregulation. We will also examine technical outcomes, including the number of artifacts and the proportion of time children are engaged in high physical movement based on accelerometry data; test the feasibility of our recruitment strategies; and test the response rate and sensitivity to change of our measures, in preparation for a future fully powered large-scale randomized controlled trial.

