### Design

We will conduct a pilot randomized waitlist-controlled field trial of the KeepCalm app (refer to the *Materials* section for details about the KeepCalm app) in which participants will either be randomized to the KeepCalm app for a period of 3 months or will be included in a waitlist and will trial the app for 3 months after an initial 3-month waiting period. In this trial, the KeepCalm app will be tested for usability, feasibility, acceptability, and appropriateness, and we will also collect some preliminary proximal and distal efficacy data to inform a future, fully powered randomized field trial.

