##### Feasibility

Feasibility of the app will be assessed through teacher and parent report using the Feasibility of Intervention Measure [66]. The measure consists of 4 items rated on a 5-point Likert scale ranging from 1 (“Completely disagree”) to 5 (“Completely agree”). The score is calculated by summing all items to yield a total score ranging from 4 to 20, with higher scores indicating greater feasibility of the app. Participants will complete this scale at the end of the trial, 3 months after baseline.

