#### Adverse Events

We will use a brief Adverse Events Checklist to be administered to teachers and parents in the treatment group weekly throughout the trial, which may include items related to teachers experiencing stress triggered by monitoring their student’s stress levels. This checklist will be reviewed by the expert advisory board for the study before trial commencement.

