### Procedure

The trial is registered at ClinicalTrials.gov (NCT05277194). After screening for eligibility, the 20 teams (at a minimum, teachers-parents and child dyads; at a maximum, teachers-parents and child-aide [or other educational team member] triads) will be randomized to the waitlist (n=10, 50%) or treatment group (n=10, 50%). The treatment (and later, the waitlist) group will use the app for 3 months. After a dyad or triad has signed up for the study, participants will complete a conferencing software-based intake meeting, during which they will be individually briefed about the KeepCalm app and complete the baseline assessments.

School personnel will then complete an in-app training session either remotely or in the classroom, during which they will receive access to the KeepCalm app, HR tracker, and accelerometer. The research team will also show or instruct teachers about how to put the HR tracker and accelerometer on the child or assist or instruct the child in putting them on themselves. Participants will download the app onto their own phones or, if they do not have an iPhone, an iPhone will be lent to them for their participation in the project. A member of the research team will also help the school personnel to customize the app for their student by showing them how to add the child’s profile and their triggers, behaviors and skills, and strategies. Standard but editable lists will be programmed into the app for each student, including evidence-based proactive and reactive strategies for reducing challenging behaviors and supporting emotion regulation [64]. All teachers recruited will have had professional development and in-class coaching in these strategies by coaches in our center. The research team will administer a fidelity assessment tool to teachers to understand their proficiency in implementing these strategies and provide additional coaching or resources for strategies, as needed.

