**Primary outcome measures**																	
	SUS^f^ (usability)	Teacher and parent														✓	
	AIM^g^ (acceptability)	Teacher and parent														✓	
	FIM^h^ (feasibility)	Teacher and parent														✓	
	IAM^i^ (appropriateness)	Teacher and parent														✓	
	Qualitative interview	Teacher, aide, and parent														✓	

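### All 20 teams use the app, but the four primary rating scales and the weekly adverse event checklist are scheduled only for the 10 treatment teams

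*Protocol article*

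**What the plan says.** **Who uses the app.** The abstract states: "We will test KeepCalm with 20 educational teams of students on the autism spectrum with challenging behaviors". Under Design, waitlist participants "will trial the app for 3 months after an initial 3-month waiting period". Procedure repeats this: "The treatment (and later, the waitlist) group will use the app for 3 months". Procedure and Power both give 10 teams per arm.

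**When the primary scales are given.** For the System Usability Scale: "This scale will be administered at the end of the trial, 3 months after baseline". For the Feasibility of Intervention Measure: "Participants will complete this scale at the end of the trial, 3 months after baseline". The Acceptability and Appropriateness sections use the same time point. None of these four sections names an arm.

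**What Table 1 schedules.** SUS, AIM, FIM, IAM and the interview each carry one tick, in the post-trial column of the treatment group. The technical and proximal efficacy rows are ticked for the treatment group only, during the trial. The adverse event row is ticked for the treatment group only, during and after the trial. The distal measures (SSQ, OS-CBS, IBR-MOAS, EDI) are ticked for both arms, at baseline and after the trial. No column covers the waitlist teams' later app use.

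**Adverse events.** The Adverse Events section describes the checklist as "to be administered to teachers and parents in the treatment group weekly throughout the trial".

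**Interview.** The Interview Feedback section and Procedure place it after study participation or app testing and do not limit it to an arm. Procedure adds that it will ask about adverse events.

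**The concern.** The Data Analysis section says that the trial is designed around users' assessment of the app rather than efficacy. A user can rate the app only after using it. A fixed point of 3 months after baseline falls at the end of use for a treatment team, but at the end of waiting for a waitlist team. The schedule therefore yields no usable primary rating from half of the teams that will use the app, although those teams are enrolled and equipped.

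The checklist has a parallel gap. Waitlist children will wear the heart rate tracker and accelerometer, and their teachers will receive the alerts, for the same 3 months. The article itself foresees app-related items on the checklist, such as teacher stress caused by the monitoring. No weekly check is scheduled for that period.

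The interview raises a consistency problem. Staff working from Table 1 would not interview waitlist teams, whereas staff working from Procedure would. Ratings and weekly reports not collected at the time cannot be recovered reliably afterwards.

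**Working it through.** **1. Timeline.** Table 1 gives both arms a baseline at the start.
- Treatment: app use in months 0 to 3; scales at month 3, the end of use.
- Waitlist: waiting in months 0 to 3 and app use in months 3 to 6. Month 3 comes before any use, and nothing is scheduled at month 6.

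**2. Table 1 columns.** The six arm columns are baseline, during-trial and post-trial, each split into waitlist and treatment. Counting column positions in the table text puts them at 2, 4, 6, 9, 11 and 14. The ticks fall as follows.

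| Row | Tick positions | Meaning |
|---|---|---|
| SUS, interview | 14 | post-trial, treatment |
| Artifact removal | 9 | during trial, treatment |
| Adverse events | 9, 14 | during and post-trial, treatment |
| SSQ | 2, 4, 11, 14 | both arms, baseline and post-trial |

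The SSQ row shows that the table does separate the arms after the trial, so the single tick on the primary rows is not an artefact of broken layout.

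**3. Teams contributing.** 10 + 10 = 20 teams use the app, which agrees with the stated total. Scheduled primary ratings come from 10/20 = 50%. The article derives no sample size from power or precision, so there is no planned figure to reproduce.

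**4. Precision of a mean score, one respondent per team.** The 95% half-width in SD units is t(0.975, n−1)/√n.
- n = 10: 2.262/3.162 = 0.715
- n = 20: 2.093/4.472 = 0.468
- Ratio 0.468/0.715 = 0.65, so the interval is about 35% narrower.

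The article gives no SD for the SUS. For assumed values:

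| Assumed SD | 10 teams | 20 teams |
|---|---|---|
| 10 | ±7.2 | ±4.7 |
| 15 | ±10.7 | ±7.0 |
| 20 | ±14.3 | ±9.4 |

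**5. Adverse events.** If no event of a given type is seen, the one-sided 95% upper bound on the team-level risk is 1 − 0.05^(1/n).
- n = 10: 25.9%
- n = 20: 13.9%

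The chance of seeing at least one event is 1 − (1 − p)^n. At an assumed risk of 5% it is 40% with 10 teams and 64% with 20. At an assumed 10% it is 65% and 88%.

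**6. Added items per respondent.** SUS 10 + three scales of 4 = 22.

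**The case against.** **Waitlist users may be heard after all.** A reader of Table 1 might infer that half the users are never asked anything. The documents do not support that. The Interview Feedback section and Procedure describe an exit interview on all four constructs, and on adverse events, without excluding the waitlist; Procedure also speaks of each participant's own testing period. This stands. What remains is a conflict between Table 1 and the text on the interview, and no scheduled rating scales or weekly checklist for waitlist app use.

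**Table 1 may cover only the randomised 3 months.** The abstract speaks of a 3-month trial, and a condensed article may leave the later schedule to the full protocol. This is a fair reason for caution about what will actually be collected. However, the article does not merely omit the waitlist phase. It fixes a time point that precludes a waitlist rating and names the treatment group for the checklist, while Design and Procedure present waitlist app use as part of the study.

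**No target is missed.** The primary analysis is descriptive and the sample size was not based on power. This stands: ten teams fail no stated criterion, and rating only the randomised treatment arm is a legitimate though less efficient choice for a pilot. Nor should one infer that the planned contrast of lowest and highest quartiles rests on two or three people. Parents and teachers both complete the scales, so ten teams give about 20 raters, or roughly 5 per quartile if pooled.

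**A background adverse event rate is not promised.** One might want the checklist during the waiting phase as a comparator. The only content described is app-specific, and no between-arm comparison of adverse events is planned, so its absence breaks no stated aim.

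**Conclusion.** The point holds as a scheduling gap. As written, the four primary scales will be collected from 10 of the 20 teams that use the app, waitlist app use has no weekly adverse event checklist, and Table 1 and the text disagree about who is interviewed.

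No analysis is invalidated, no comparison is biased and no stated number is wrong. The loss is in precision and in the capture of adverse events: a half-width of 0.72 SD instead of 0.47 SD, and a zero-event upper bound of 25.9% instead of 13.9%.

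These figures assume independent teams, no dropout and one respondent of each type per team, so they are a best case. A teacher may take part with two students. The effective number of teacher ratings is then below the number of teams, and the gain is smaller where a waitlist team shares its teacher with a treatment team, which the article does not rule out.

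**What to change.** 1. In the Usability, Feasibility, Acceptability and Appropriateness sections, replace the fixed time point with the end of each team's own 3-month app period: month 3 for treatment, month 6 for waitlist.
2. Extend the weekly adverse event checklist to the waitlist app phase in the Adverse Events section and in Table 1.
3. Add a waitlist app-phase column to Table 1 carrying the four scales, the checklist, and the app and technical metrics that are recorded automatically.
4. Reconcile the interview row of Table 1 with Interview Feedback and Procedure, stating whether waitlist teams are interviewed after their app use.
5. Report primary outcomes by arm and pooled over all teams that used the app, since the two arms use it in different months.
6. Leave the 3-month between-arm comparison of the distal measures as it is.

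**Cost.** One 22-item questionnaire set for each teacher and parent, and a brief weekly checklist for 3 months, in 10 teams already enrolled; their exit interview (30 minutes) as well, if not already intended. No new participants are needed. Repeating the distal measures at month 6, adding classroom observation, or giving the checklist during the waiting phase would be optional extras at further cost; this point does not depend on them.
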